### Dynamic balance ability

Was assessed using the Biodex Stability System (BSS; Biodex Medical Systems, Shirley, NY, USA), which features a 360° rotating platform with a maximum tilt of 20° [24]. Specialized software (Biodex, Version 1.32) used indices such as the Overall Stability Index (OSI), Anterior-Posterior Stability Index (APSI), and Medial-Lateral Stability Index (MLSI) for evaluation. APSI and MLSI represent platform displacements in the sagittal (Y) and frontal (X) planes, respectively, while OSI is their composite score (OSI = [(Σ(0– Y)² + Σ(0– X)² / samples)]^0.5).[25] Lower scores indicated better balance. Testing occurred in a quiet setting. Participants stood barefoot, one-legged, with eyes open, knees bent 15°, arms down, and feet on markers. After a 1-minute adaptive training and three practice trials to minimize anxiety and learning effects, the official test involved an 8-level stability test (most stable level) [26]. Each 20-cycle had automatic tilting. Three trials were conducted with a 10-second rest between them, and the average score was computed.

### Proactive balance ability

Was assessed using the Timed Up and Go Test (TUG) [27]. Participants sat in a chair with a backrest, seat height of approximately 45 cm, and armrest height of approximately 20 cm, leaning back against the chair with feet flat on the ground. Upon hearing “start,” participants rose from the chair, walked as quickly and safely as possible forward, crossed a marker line 3 m from the chair, turned around, and returned to sit back against the chair. The time from the “start” command to sitting back down was recorded. After one practice trial, two test trials were conducted, and the average of the two trials, rounded to two decimal places, was used in the analysis.

### Reactive balance ability

Was evaluated using the Push and Release Test (PRT), which assessed participants’ postural response to suddenly releasing an examiner’s hand placed on their back [28]. Participants stood in a comfortable position with their eyes open and pushed backward against the examiner’s palm. Upon sudden release, participants had to regain balance (by taking steps backward until they reached a stable position). The examiner ensured the participants’ safety during testing. For rating, the actual number of steps taken to regain balance (excluding steps to reposition feet) was measured (0 = 1 step, 1 = 2–3 small steps independently, 2 = ≥ 4 steps independently, 3 = steps with assistance, 4 = fall or inability to stand without assistance).

### Daily living balance ability

Was assessed using the Balance in Daily Living (BDL) scale recently developed by French scholars [29]. Participants were asked to complete seven daily household tasks requiring postural adaptation and multitasking. Each task was scored as follows: 1 = normal (no instability), 2 = adequate (patient uses safe strategies, anticipatory adaptation, no instability), 3 = abnormal (patient uses reflexive adaptation strategies, corrective adaptation, fall avoidance strategies, mild instability), and 4 = very abnormal (ineffective postural adaptation reflexes, severe instability). No score was assigned if a task could not be performed due to reasons other than balance impairment.

### Grip strength

Is assessed using a CAMRY^®^ electronic dynamometer. During the test, participants maintain neutral shoulder rotation and adduction, 90° elbow flexion, and neutral wrist and forearm positions. Participants perform three maximum-effort trials with verbal encouragement, with a 1-minute rest between each trial. The mean grip strength (HGS) is calculated as the average of the three measurements in kilograms.

### Manual dexterity

Is objectively evaluated using the Jebsen-Taylor Hand Function Test (JHFT), which measures hand function in daily living activities. JHFT comprises seven subtests: (1) writing a standard sentence, (2) turning over five cards, (3) picking up and replacing small objects, (4) simulating eating with a spoon and five beans, (5) stacking four raw beans on a board, (6) flipping five large empty cans, and (7) flipping five full cans. The completion time for each subtest is recorded to the nearest second and summed to obtain a total score. JHFT is a reliable and valid assessment tool with established psychometric properties in older adults and is widely used to assess hand dexterity in various contexts [30]. 

### Life-space mobility

Is evaluated using the Life-Space Assessment (LSA). This scale assigns scores based on the range of activities (1–5 points for bedroom, home, outside home, community, and beyond the community), frequency of activities (1.5–4.5 points for 1 week, 2–3/week, 4–6/week, and daily), and independence (1, 1.5, and 2 points for assistance, assistive devices, and no assistance, respectively). The LSA total score is calculated as the sum of area scores (area score = range × frequency × independence), ranging from 0 to 120 points, with higher scores indicating greater mobility [7]. 

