### Randomization, allocation concealment, and blinding

Four rural communities in Huzhou, Zhejiang Province, were randomly selected to ensure comparability regarding economic development, cultural practices, and infrastructure. A minimum separation distance of 5 km between communities was maintained to minimize contamination risk. The investigator prepared slips labeled “Intervention groups (a)(b)(c)” and “control group” and placed them in sealed envelopes. Representatives from the four communities randomly selected envelopes and were assigned to the four groups on a 1:1:1:1 ratio. Research assistants received intervention information via sealed envelopes, while outcome evaluators and data analysts remained blinded to the intervention details. Due to the nature of the intervention, blinding participants was not feasible.

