### Primary outcomes

Primary outcome assessments focused on multidimensional balance ability (static, dynamic, proactive, reactive, and daily living balance), hand function (grip strength and manual dexterity), and life-space mobility.

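### The printed Life-Space Assessment weights give a maximum of 135, which contradicts the stated 0 to 120 range; the two must be reconciled before this primary outcome is scored

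*Protocol article*

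**What the plan says.** The Life-space mobility section of the protocol article gives three sets of weights:

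- Range: "range of activities (1–5 points for bedroom, home, outside home, community, and beyond the community".
- Frequency: "frequency of activities (1.5–4.5 points for 1 week, 2–3/week, 4–6/week, and daily". Only the two end values are printed; those for the two middle categories are not.
- Independence: "independence (1, 1.5, and 2 points for assistance, assistive devices, and no assistance, respectively".

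The total is the sum of the area scores, with the product rule and the scale limits stated together: "area score = range × frequency × independence), ranging from 0 to 120 points".

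The Primary outcomes section closes its list with "hand function (grip strength and manual dexterity), and life-space mobility", so the LSA total is one of the primary measures. No other section gives LSA weights or a different range.

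**The concern.** The article states both the algorithm and the limits of the scale, so each can be checked against the other, and they disagree. This is not a detail left to a fuller document: the rule is printed in full and contradicts its own range.

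Two things are at stake. First, a programmer who follows the printed weights can obtain totals above 120, and a range check set at 0 to 120 would reject totals that follow the printed rule exactly. Second, scores computed with the printed weights would not be on the scale the article claims, so they could not safely be set beside LSA scores from a 0 to 120 scale.

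**Working it through.** **Inputs** (all from the Life-space mobility section): range weights 1, 2, 3, 4, 5, with sum 15; top frequency weight 4.5; top independence weight 2; stated maximum 120.

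**Step 1. Try to reproduce the stated maximum.** Maximum = sum of range weights × top frequency × top independence = 15 × 4.5 × 2 = 135. This is 135/120 = 1.125 times the stated figure, or 12.5% above it. The unprinted middle frequency weights play no part.

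**Step 2. Try other readings of the rule.**

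- Highest area only: 5 × 4.5 × 2 = 45.
- Areas 1 to 4, or areas numbered 0 to 4: 10 × 4.5 × 2 = 90.
- Areas 2 to 5: 14 × 4.5 × 2 = 126.
- Independence capped at 1.5: 15 × 4.5 × 1.5 = 101.25.

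None gives 120.

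**Step 3. Solve for the element that would give 120.**

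- Frequency: 120/(15 × 2) = 4.
- Independence: 120/(15 × 4.5) = 1.78, which is not one of the listed values 1, 1.5 and 2.

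A top frequency weight of 4 is therefore the simplest single change that restores 120. That is arithmetic, not proof of what was intended.

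**Step 4. Size of the discrepancy for one person.** Assume that the printed frequency weights are 1.5, 2.5, 3.5, 4.5 and the intended ones 1, 2, 3, 4. Each visited area then gains 0.5 × range × independence, so

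excess = 0.5 × sum of (range × independence) over the areas visited.

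The excess runs from 0 (no area visited) to 0.5 × 15 × 2 = 15 (all five areas, unaided).

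Example: an unaided person is out daily in areas 1 to 4 and goes beyond the community 4–6 times a week.

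- Printed weights: 10 × 4.5 × 2 + 5 × 3.5 × 2 = 90 + 35 = 125, which is above 120.
- Weights 1 to 4: 10 × 4 × 2 + 5 × 3 × 2 = 80 + 30 = 110.

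**Step 5. What happens to changes in score.** Same assumption. The starting profile is areas 1 to 3 daily, area 4 at 2–3 times a week and area 5 at the lowest frequency, unaided: 89 with the printed weights, 74 with 1 to 4.

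- One frequency category higher in area 4: 97 − 89 = 8 against 82 − 74 = 8. No difference.
- Area 5 newly reached, against not reached: 89 − 74 = 15 against 74 − 64 = 10.
- Independence from 1.5 to 2 in all areas: 22.25 against 18.5.

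The two rules agree when only frequency changes within areas already visited. They differ when a new area is reached or independence changes.

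**Step 6. Scale at arm level.** For unaided people, reaching area 5 carries an excess of 0.5 × 5 × 2 = 5 points. If two arms differed by 10 percentage points in the share reaching area 5, and in nothing else that affects the excess (an assumption), the mean difference would move by 0.10 × 5 = 0.5 points.

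**The case against.** The strongest reply is that this may be only a misprint. The article summarises a named, cited instrument, and the scoring form itself is not shown. If the form in use is scored correctly to 120, no participant's score is wrong. The Data Availability section says no datasets were generated or analysed, so nothing shows that any form has been mis-scored. This stands. The documents establish a contradiction, not an error in data.

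A reader might go further and infer that the outcome will be mis-scored and the arm comparison distorted. The documents do not support that. Mis-scoring follows only if the printed weights are used. Even then, one rule applies to all four arms, and the article says that "outcome evaluators and data analysts remained blinded to the intervention details". Arms with the same distribution of mobility would have the same distribution of scores under either rule. What can change is the size of a real difference.

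It can also fairly be said that the most striking contrast, 15 points against 10 for a newly reached area, is an extreme single transition and depends on assumed weights. Eligibility requires independent walking for at least 15 minutes. If most participants are therefore unaided (an assumption), the excess is 15 points for those who reach all five areas and 10 for those who reach areas 1 to 4. Much of it is then a shift common to all arms. This also stands.

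Finally, the LSA is one of eight measures listed as primary, and the Sample size section rests on a posture-control study, so no power figure changes. That limits the consequence but does not remove the contradiction.

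**Conclusion.** The point holds as an internal contradiction in the scoring rule of a primary outcome. The printed weights give 135, the stated maximum is 120, and none of the readings tried reconciles them. This rests on the article's own figures alone.

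The consequence is conditional. If the printed weights are applied, totals can exceed the stated scale. The excess of 0 to 15 points per person assumes intended weights of 1 to 4 and printed weights of 1.5 to 4.5, both in unit steps. The excess is not constant across people, so the size of a real arm difference could change, as could comparability with LSA scores on a 0 to 120 scale. Bias towards an arm, or a spurious difference between arms of equal mobility, is not shown.

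The documents do not settle whether the weights or the range is wrong. The matter is small in extent, but it should be settled before any LSA total is computed.

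**What to change.** Before scoring, compare all the frequency weights, including the two that are not printed, with the form cited in the Life-space mobility section. Then do one of the following:

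- correct the frequency weights so that the formula gives 0 to 120 (top weight 4, other weights unchanged); or
- if 1.5 to 4.5 is intended, restate the range as 0 to 135 and say that the scores are not on a 0 to 120 scale.

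Print all four frequency weights, and set the data-entry range check to the corrected maximum. If any forms have already been scored with the wrong weights, recalculate them from the item responses.

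The cost is a one-line correction and, if needed, a recalculation. Design, allocation, data collection and sample size are unaffected.

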Life-space mobility (LSM) is a comprehensive and dynamic measure that reflects the interaction between individual functions, environment, and society [7]. Compared to laboratory-based assessments, LSM provides a more accurate reflection of real-life physical activities and functions, serving as a strong predictor of adverse outcomes such as falls, hospitalization, and premature death [8]. According to the Webber framework, physical performance, including strength and balance, significantly influences LSM [9]. Kuspinar et al. found that lower walking speed, TUG test scores, and grip strength are associated with reduced LSM [8]. Uchida et al. confirmed that psychological factors, such as fear of falling, depression, and anxiety also impact LSM [10], while poor infrastructure, uneven sidewalks, and noisy traffic in rural areas contribute to mobility disorders, restricting life-space mobility [11]. 

Somatic balance ability encompasses static/dynamic steady-state balance, active balance, and reactive balance [12]. Static balance training involves maintaining independent static postures and low-intensity stability exercises. Ni’s research demonstrated significant improvements in SPPB and One Leg Stand Test scores among community-dwelling older adults after sensory-based static balance training [13]. Granacher et al. reported that an 8-week home-based static gait balance program enhanced active balance and lower limb strength in healthy older adults individuals aged 60-72 [14]. Dynamic balance training aims to improve high-intensity stability and coordination. Hagovska et al. observed significant improvements in walking speed, step length, and body posture control after ten weeks of dynamic balance training [15]. While both static and dynamic training improves balance, their combined effect on multidimensional balance and LSM remains understudied.

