### Data analysis

SPSS 26.0 software was used for statistical analysis, with a significance level set at *p* < 0.05. Initially, the Shapiro-Wilk test will be employed to assess the normality assumption for quantitative data. Based on these results, appropriate statistical methods will be selected to compare participants’ demographic and other baseline characteristics before the intervention. If the data are normally distributed, an independent-sample t-test will be utilized; otherwise, the Mann-Whitney *U* test will be applied. The primary outcome measures, continuous variables, were analyzed using generalized estimating equations (GEEs). In cases of significant interactions between group and time factors, a simple effects analysis will be conducted to elucidate the sources of the differences. If the simple effects analysis of time factors yields significant results, post hoc tests will be performed using the Sequential Bonferroni Procedure to identify specific time points of substantial differences. Secondary outcomes included descriptive statistics on exercise adherence after intervention.

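### The printed Life-Space Assessment frequency classes leave a gap at or just below once a week, and the printed weights give a maximum of 135 rather than the stated 120

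*Protocol article*

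**What the plan says.** The Primary outcomes section lists "hand function (grip strength and manual dexterity), and life-space mobility" among the primary outcomes. The Life-space mobility section then prints a complete scoring rule:

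- Zone weights: "1–5 points for bedroom, home, outside home, community, and beyond the community".
- Frequency classes and weights: "frequency of activities (1.5–4.5 points for 1 week, 2–3/week, 4–6/week, and daily". Only the two end weights are given.
- Independence weights: "independence (1, 1.5, and 2 points for assistance, assistive devices, and no assistance, respectively".
- Combination: "area score = range × frequency × independence", summed over the zones.
- Total: "ranging from 0 to 120 points, with higher scores indicating greater mobility".

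Under Data analysis the score is treated as continuous: "The primary outcome measures, continuous variables, were analyzed using generalized estimating equations (GEEs".

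**The concern.** A rule that multiplies three weights and sums over zones works only if every response falls into exactly one class. The frequency list starts at a label printed as 1 week and goes straight to two to three times a week. One kind of ordinary answer therefore has no place, and its score is left to whoever fills in the form. The two outer zones matter most because they carry the largest multipliers, 4 and 5.

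The same sentence does not reproduce its own stated range, so it cannot be relied on to settle the doubt about the classes. At stake is the definition of a primary outcome. Two people following the article could give the same participant different totals, and a move across the once-a-week boundary might or might not count as change.

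**Working it through.** **Inputs**, all from the Life-space mobility section: zone weights 1, 2, 3, 4, 5 (sum 15); frequency weights from 1.5 to 4.5 over four classes; independence weights 1, 1.5 and 2; stated range 0 to 120.

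**Step 1: try to reproduce the stated maximum.** Maximum = sum of zone weights × top frequency weight × top independence weight.

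- Printed weights: 15 × 4.5 × 2 = 135. The stated 120 is not reproduced; 135/120 = 1.125, so the printed weights overshoot by 12.5%.
- Top weight needed for 120: 120 / (15 × 2) = 4.

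The stated range fixes only the top weight. Four unit steps ending at 4 would be 1, 2, 3, 4, with a lowest weight of 1. A lowest weight of 1.5 with a top of 4 and unequal or smaller steps would also give 120. The lowest weight is therefore taken as 1 to 1.5 below.

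**Step 2: test whether the classes are exhaustive.**

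| Reading of the first label | Less than weekly | Exactly weekly | 2–3 times a week or more |
|---|---|---|---|
| Once a week | no class | first class | covered |
| Less than once a week | first class | no class | covered |
| Once a week or less | first class | first class | covered |

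The two literal readings each leave a gap. Only the third closes it, and the article does not state it.

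**Step 3: size of the gap on the once-a-week reading.** A less-than-weekly zone is coded either 0 or with the lowest weight. Difference = zone weight × lowest frequency weight × independence weight.

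| Zone | Independence | Lowest weight 1 | Lowest weight 1.5 |
|---|---|---|---|
| 5 | no assistance (2) | 5 × 1 × 2 = 10 | 5 × 1.5 × 2 = 15 |
| 5 | device (1.5) | 5 × 1 × 1.5 = 7.5 | 5 × 1.5 × 1.5 = 11.25 |
| 5 | assistance (1) | 5 × 1 × 1 = 5 | 5 × 1.5 × 1 = 7.5 |
| 4 | no assistance (2) | 4 × 1 × 2 = 8 | 4 × 1.5 × 2 = 12 |

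These are differences for a single zone. If zones 4 and 5 are both affected, the unassisted total differs by 10 + 8 = 18 to 15 + 12 = 27 points.

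**Step 4: size of the gap on the less-than-once-a-week reading.** An exactly weekly zone could be put in the first or the second class. With unit steps between classes (an assumption, since the intermediate weights are not printed), the unassisted difference is 5 × 1 × 2 = 10 points in zone 5 and 4 × 1 × 2 = 8 in zone 4.

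**The case against.** The best defence is that the first label is visibly malformed: the next two classes carry a slash and this one does not, so it may be a shortened or damaged form of something sensible. That is fair, and a symbol lost in text extraction cannot be excluded. Comparison signs do survive in the Static balance and Reactive balance sections, so loss is not evident either. More to the point, restoring a less-than sign only moves the gap to exactly weekly visits. The defence succeeds only if the label meant once a week or less, and even then the wording needs clarifying. It does nothing for 135 against 120.

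A second defence is that the article cites an established instrument, and assessors may score from its form and not from this sentence. This also has force: nothing shows that any form has been mis-scored. But the article does not leave the scoring to the instrument. It prints classes, weights, formula and range, and these do not fit together.

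Three stronger inferences might tempt a reader, and the documents do not support them:

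- **That one extra trip over some number of weeks moves the score by 15 points.** The article gives no recall period for the LSA, so the boundary cannot be expressed as a count of trips.
- **That the gap affects many participants.** The Introduction says that "noisy traffic in rural areas contribute to mobility disorders, restricting life-space mobility", but this is general background. Eligible participants must be able to walk independently for at least 15 minutes, and no distribution of visit frequencies is given. Any assumed share of miscoded forms would be a guess.
- **That local coding habits would become an arm difference because each community is one arm.** Data collection and management describes a single team with standardised training, and the randomisation section describes blinded outcome evaluators. No separate assessors for each community are mentioned. A rule applied in the same way at all visits would also largely drop out of the group-by-time comparison, except for participants who cross the boundary.

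**Conclusion.** The point stands as a badly fixed scoring rule for a primary outcome. On either literal reading the frequency classes are not exhaustive, and the printed weights contradict the stated range (135 against 120).

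For an unassisted participant whose less-than-weekly visits are coded 0 instead of the lowest class, the score differs by 10 to 15 points for zone 5 and 8 to 12 for zone 4. This rests on two assumptions: that 0 is the alternative code, on which the article is silent, and that the lowest weight lies between 1 and 1.5. The top of the range uses a printed weight from a set that is itself in doubt.

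How many participants are affected is unknown. No bias between arms is shown. The correction is worth making before the LSA is scored for analysis, because the rule chosen decides whether a move across the boundary counts as change.

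**What to change.** Correct the scoring sentence in the Life-space mobility section:

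1. State frequency classes that are exhaustive and do not overlap, so that less-than-weekly and exactly weekly visits each have one defined place, and say how an unvisited zone is scored.
2. Print the weight of every class. Reconcile classes and weights with the version of the instrument cited as reference 7 and with the 0–120 range. If the version in use really has a top weight of 4.5 with the other weights as printed, the stated maximum must change.
3. Use one scoring sheet in all four communities at T0 to T4.
4. Apply it to any T0 forms already completed, where the visit frequency was recorded in enough detail.

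The cost is one corrected line and one sheet. No new measurements are needed. Recoding is possible only where the raw frequency was written down, which is a reason to do it early.
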